## Abstract

**Background::**

Peripheral artery disease affects over 236 million people globally and the
classic symptom is intermittent claudication (IC) which is associated with
reduction in physical activity. The evidence that supervised exercise
programmes (SEPs) improve pain-free and maximal walking distance is
irrefutable. However, adherence rates are low with exercise-related pain
cited as a contributing factor. National and international guidelines
recommend exercising at a moderate to maximal level of claudication pain to
improve walking ability; however, exercising pain-free or at mild
claudication pain has been shown to achieve this outcome. There is limited
evidence that compares the relative effects of exercise prescribed at
different levels of claudication pain.

**Objective::**

The objective of this study is to directly compare the effects of exercise
prescribed at three different levels of claudication pain on walking
performance.

**Design::**

This study will be a single-centre randomised controlled trial.

**Methods::**

Based on an *a priori* power calculation, 51 patients with IC
will be allocated to 24 weeks of twice-weekly pain-free (PF), moderate pain
(MOD-P) or maximal pain (MAX-P) exercise. The PF group will cease exercise
at the onset of claudication (1 on the 0–4 IC rating scale), the MOD-P group
will stop once moderate pain is reached (2 on the rating scale) and the
MAX-P group will stop once maximal pain is reached (4 on the rating
scale).

**Analysis::**

Outcome measures will be assessed at baseline, 12 and 24 weeks adopting an
analysis of covariance (ANCOVA) to compare MWD across three time points. The
primary outcome for the trial will be change in maximal treadmill walking
distance at 12 and 24 weeks.

**Registration::**

Trial registration number: NCT04370327.

## Introduction

Peripheral artery disease (PAD) is characterised by atherosclerotic lesions of the
arteries in the lower limbs, resulting in a reduction in blood flow.^
1
^ Globally, it is estimated that 236 million people are living with PAD, with
the number of cases increasing.^
2
^ A classic symptom of PAD is intermittent claudication (IC), characterised by
ischemic muscle pain in the leg precipitated by exertion and relieved by
rest.^3,4^ PAD is
associated with various comorbidities such as diabetes mellitus, hypertension and
dyslipidaemia, as well as reductions in physical function, quality of life and
balance.^3,5,6^ National and
international guidelines^4,7^
recommend exercise therapy as the first-line treatment for patients with IC,
generally advocating 2 h per week of a supervised exercise over a 3-month period,
with patients being encouraged to exercise to the point of moderate or maximal pain.
Exercise therapy, via supervised exercise programmes (SEPs), is supported by
high-quality evidence for its clinical and cost-effectiveness, costing less than a
tenth of angioplasty.^8,9^

Despite the plethora of evidence demonstrating the benefits of SEPs, less than half
of the vascular units in the United Kingdom have access to one and patient uptake
rates are low.^10,11^ One of the primary reasons for poor adherence may be the level
of pain prescribed during SEPs. Indeed, exercise-induced pain is a major barrier to
physical activity in this population,^
12
^ and the level of pain prescribed during SEPs influences completion rates.^
13
^ When exercise is prescribed at higher levels of pain, completion rates are
lower. However, current evidence and guidelines advocate exercising at moderate to
maximal pain,^7,14–16^ despite evidence to the
contrary, suggesting that mild- or pain-free exercise improves walking
ability.^17–20^ The lack of adequately
powered, randomised clinical trials investigating the effects of exercise prescribed
at differing levels of claudication pain has also been highlighted in a recent
scientific statement from the American Heart Association.^
16
^ As such, it remains unclear which level of claudication is optimal for
improving walking performance in patients with IC.^
21
^ The aim of this trial is to directly compare the effects of exercise
prescribed at different levels of claudication [pain-free (PF), moderate pain
(MOD-P) and maximal pain (MAX-P)] on (1) maximal and pain-free walking distance; (2)
adherence; (3) acceptability, tolerability and enjoyment of the exercise
intervention; (4) walking behaviour and physical activity; and (5) barriers and
quality of life. It is cautiously expected that maximal pain will lead to greatest
improvements in walking performance.

## Methods and analysis

This study is a single-centre randomised controlled trial. Participants will be
randomly allocated to 24 weeks of PF, MOD-P or MAX-P exercise with outcomes measured
at baseline (visit 1), 12 weeks (visit 2) and 24 weeks (visit 3). All sessions will
be supervised by a qualified exercise professional within an existing community
pathway. As this programme duration is longer than suggested in current UK
guidelines, outcomes will be measured at 12 and 24 weeks to ensure generalisability
of the findings to UK SEPs.

### Setting

The trial will be conducted in one centre under the Heartbeat Northwest
Cardiovascular Prevention and Rehabilitation charity programme. Patients will
attend an SEP from the choice of three Heartbeat cardiovascular rehabilitation
sites across Lancashire, UK (Preston, Chorley and Blackpool). Testing will also
be conducted at these locations.

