### Randomisation and blinding

The random allocation sequence will be generated by the trial statistician on a
1:1 basis using a computer program random number generator. To ensure allocation
concealment, researchers will request randomisation from the principal
investigator on completion of all baseline assessments using a sealed, opaque,
sequentially numbered envelope. All outcome assessors will be blinded as will
the trial statistician. Exercise professionals delivering the interventions
cannot be blinded; however, they will not be involved in data analysis or
reporting.

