### Outcome assessments

Clinical examination will include a review of past medical history and current
medications, height, weight and cardiovascular risk factor assessment, that is,
resting blood pressure and smoking status. Walking behaviour and physical
activity will be recorded over a 7-day period, at baseline (1 week prior to
commencing the SEP) and at 12 weeks and 24 weeks using an ActiGraph GT9X link
activity monitor (ActiGraph, Pensacola, FL, USA). A valid wear time is defined
as 4>days of >10 h of wear. Periods of >60 min of consecutive zero
reading will be considered as non-wear time. Activity intensities will be
assigned adopting cut points on those validated in coronary artery disease populations,^
25
^ with light, moderate and vigorous classified as <1800 counts/min,
1800–3799 counts/min and >3800 counts/min, respectively. Sedentary bouts will
be defined as periods of wear time exceeding 60 min at <150 counts/min.

A graded treadmill walking test will be performed to determine MWD and PFWD. The
treadmill protocol will consist of a constant speed of 3.2 km/h and incremental
gradient beginning at 0% increasing 2% every 2 min, for a maximum of 15 min^
26
^ and will be conducted in accordance with published recommendations for
implementation, ensuring standardisation.^
27
^ PFWD will be recorded at the point at which the patient first indicates
the onset of claudication pain. MWD will be recorded when the patient can no
longer continue due to claudication pain.

Adherence and compliance will be determined by recording the number of training
sessions attended and successfully completed in accordance with the exercise
protocol. Drop-out from the SEP will also be documented for all study groups in
addition to the reason for drop-out, where provided voluntarily by
participants.

Quality-of-life measures will be recorded using disease-specific questionnaires.
The King’s College Vascular Quality of Life, a 25-item questionnaire with five
domains (pain, symptoms, activities, social and emotional), and the Walking
Impairment Questionnaire (WIQ) will be used to assess the perceived impact of
claudication.^28,29^ Personal and environmental barriers to physical
activity in PAD will be based on the studies by Barbosa *et al.*^
12
^ and Cornelis *et al.*^
30
^ A 5-point ordinal scale (never, seldom, sometimes, frequently, always)
will be used to assess the limiting character of each barrier (see Table 1).^
30

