### Sample size

Power analysis performed in G*Power^
31
^ showed that 39 patients (total) would be needed to attain statistical
significance. Based on previously published data investigating a UK-based SEP
that adopted a similar exercise circuit^
32
^ and converting the interquartile range to standard deviation,^
33
^ a median change in MWD of 143 m and a pooled standard deviation of 111.3
m was calculated. A power of 90% and a significance level of 5% were assumed. A
drop-out of approximately 30% will be allowed, yielding a required sample size
of 51 patients (17 per group) to be randomised.

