### Data analysis

The primary endpoint for the statistical analysis is the change in MWD from
baseline to 12 and 24 weeks. An analysis of covariance (ANCOVA) will be used to
compare MWD across three time points with baseline MWD as a covariate. Post hoc
analysis for the main effects and interactions will be assessed using a
Bonferroni adjustment. Group differences will be compared using simple main
effects. Secondary outcomes such as PFWD distance will be evaluated adopting the
same approaches. Qualitative data will be analysed using inductive thematic
analysis whereby themes are identified from the transcripts.^
35
^

Data will be entered into SPSS (IBM, New York, USA) by a single investigator who
will maintain the overall responsibility for data quality. The primary and
secondary outcome analyses will be conducted at the conventional (two-sided) 5%
alpha level. Where parametric data distribution allows, partial eta squared
values will also be reported. To reduce the risk of false-positive claims,
secondary analyses will be considered exploratory if non-significant results are
obtained from the primary analysis. All analyses will be performed on an
intention-to-treat basis. All data will be summarised and reported in accordance
with the Consolidated Standards of Reporting Trials (CONSORT) guideline, the
template for intervention description and replication (TIDieR) and recently
published recommendations.^36–38^

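### Exercise and treadmill testing run at three patient-chosen sites, but site enters neither the stated allocation nor the primary model: a small, avoidable loss of precision

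*Protocol article*

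**What the plan says.** The Setting section states "The trial will be conducted in one centre under the Heartbeat Northwest" programme, and that patients "attend an SEP from the choice of three Heartbeat cardiovascular rehabilitation" sites (Preston, Chorley and Blackpool). The sentence beginning "Testing will also" places outcome testing at the same locations.

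Randomisation and blinding describes a sequence generated on a "1:1 basis using a computer program random number generator", issued in sealed, opaque, numbered envelopes once baseline assessments are complete. It names no stratification by site.

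Data analysis specifies an ANCOVA to "compare MWD across three time points with baseline MWD as a covariate". No other covariate is named.

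**The concern.** Patients choose their site, so case mix may differ between sites. The exercise is individually prescribed and supervised by staff, so delivery may differ too. The primary outcome is measured on the treadmill at the site. Baseline MWD absorbs stable differences in patients and equipment. It does not absorb differences in how well the programme is delivered or how patients respond to it, and those feed directly into change in MWD.

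With about 17 patients per arm spread over three sites, arms can by chance be unevenly distributed. An unadjusted comparison then carries part of the site difference as random error. At stake is precision, in a trial with little to spare.

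**Working it through.** **The plan's own figures.** Sample size gives "a median change in MWD of 143 m and a pooled standard deviation of 111.3" m, with 90% power and 5% significance (two-sided, per Data analysis).

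- Per arm: 2 × (1.960 + 1.282)² × (111.3/143)² = 2 × 10.51 × 0.606 = 12.7, so 13; three arms give 39, as stated.
- Randomised: 39 × 1.3 = 50.7, so 51, as stated.
- After the planned 30% loss: 51 × 0.70 = 35.7, so about 36 analysed. This is the number used below.

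**How uneven can arms be across sites?** The calculation used 20,000 random permutations of 51 patients into arms of exactly 17, ignoring site. Numbers per site are not in the protocol and are assumed.

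| Patients per site | Chance that some site has two arms differing by 5 or more | Chance that some arm is absent from a site |
|---|---|---|
| 17/17/17 | 45% | 0.2% |
| 25/16/10 | 42% | 3% |
| 30/14/7 | 38% | 14% |

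If one site differs from the others by D in MWD change, a 5-patient imbalance shifts an arm contrast by D × 5/17. That is about 7, 15 and 29 m for assumed D of 25, 50 and 100 m, or 5%, 10% and 21% of 143 m. The shift has no preferred direction.

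**Variance of an arm contrast.** Assume 36 analysed, 12 per arm, three equal sites, and site effects of −τ, 0 and +τ. These are in SD units and represent what remains after baseline adjustment.

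- The mean squared site effect is 2τ²/3.
- Equal arms, site ignored: variance = (2/12) × (1 + (2τ²/3) × 36/35).
- Stratified by site and adjusted, with perfect balance: variance = 2/12, so SE = 0.408 SD whatever τ is.

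| τ | Step in metres (τ × 111.3) | Site ignored: variance relative to 2/12 | Reduction from stratifying and adjusting |
|---|---|---|---|
| 0 | 0 | 1.000 | 0% |
| 0.25 | 28 | 1 + 0.0417 × 1.029 = 1.043 | 1 − 1/1.043 = 4% |
| 0.50 | 56 | 1 + 0.1667 × 1.029 = 1.171 | 1 − 1/1.171 = 15% |

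Incomplete blocks and dropout spoil the perfect balance a little, so 12 to 15% is the fair range for the last row.

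**If allocation is unrestricted.** Simulated SEs with site ignored are 0.417 to 0.423 at τ = 0, 0.432 at τ = 0.25, and 0.453 to 0.460 at τ = 0.5. Set against 0.408, the reductions are 4 to 7%, 11% and 19 to 21% [for example, 1 − (0.408/0.432)² = 0.11]. Part of each comes from equalising arm sizes, which needs no site information; at τ = 0 all of it does.

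**Site in the model without stratified lists** (simulated, unrestricted allocation). The SE goes from 0.423 to 0.435 at τ = 0 (0.435/0.423 = 1.03), from 0.432 to 0.435 at τ = 0.25, and from 0.460 to 0.436 at τ = 0.5. With equal arms at τ = 0.25 it goes from 0.414 to 0.421.

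**Power.** Take 13 per arm, a pairwise t test, 111.3 m as the total SD, and arms balanced within site. Adding site (2 degrees of freedom) changes power from 0.881 to 0.879 if site explains none of the outcome variance, 0.895 at 5%, 0.910 at 10% and 0.938 at 20%. For reference, τ = 0.25 corresponds to 0.0417/1.0417 = 4% and τ = 0.5 to 0.1667/1.1667 = 14%.

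**The case against.** Leaving site out of a small trial run by one programme is defensible. The treadmill test follows published recommendations for "implementation, ensuring standardisation", and baseline MWD already removes two plausible sources of site difference, patient mix and equipment. What remains may be close to zero, and nothing in the protocol measures it. The article may also condense a fuller protocol that describes blocking. These arguments stand as limits on size. They do not remove the point, because the article does state an allocation method and a covariate, and describes three sites that appear in neither.

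Some stronger readings are tempting but unsupported:

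- A reader might infer that the plan uses simple, unrestricted randomisation. The article does not say so, and it plans 17 per group. The distinction matters: the chance that some arm has 2 or fewer patients at a site (equal sites) is about 34% if unrestricted but about 15% with arms fixed at 17.
- A reader might infer a saving of a fifth or more of the variance. That needs both unrestricted allocation and 56 m steps, and it credits site with the gain from equal arm sizes.
- A reader might infer bias or false-positive risk. Imbalance under random allocation gives neither.
- A reader might call the single-centre label a contradiction. The Setting section openly explains one centre with three locations.

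**Conclusion.** The point holds as a minor matter of efficiency. Three sites deliver the exercise and measure the outcome, and neither the stated allocation nor the stated model uses site. With equal arms and 36 analysed, the recoverable variance is about 0%, 4% or 12 to 15% for site steps of 0, 28 or 56 m, and somewhat more if allocation is unrestricted. These site differences, the equal site sizes and the use of 111.3 m as the unit are assumptions, and the true effect is probably towards the lower end. Stratifying and adjusting together is essentially never worse than the plan and sometimes better. No conclusion of the trial would be invalid without it.

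**What to change.** In Randomisation and blinding, generate one 1:1:1 list per site with randomly varying blocks of 3 and 6, held in three envelope sets. State that allocation is requested only after the participant's site is fixed at baseline testing. The article implies this order, since baseline assessment at the sites precedes randomisation, but does not say it outright. In Data analysis, add site as a fixed factor beside baseline MWD.

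The cost is two more envelope sets, 2 degrees of freedom and slightly more predictable allocation within site, which random block sizes concealed from recruiting staff keep in check.

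If recruitment has already begun on an unstratified list, adding site to the model alone is optional. It helps only if site differences are sizeable (near 0.5 SD) and otherwise widens the SE by up to about 3%. That choice should be made before outcome data are seen by arm.

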### Study registration

The trial was prospectively registered on ClinicalTrials.gov (NCT04370327). Any
amendments required to this protocol will seek approvals from the research
ethics committee before implementation and will be fully reported in the final
trial report.

### Participants

Patients recently diagnosed with IC by a vascular surgeon or vascular specialist
nurse will be referred to the SEP and screened for study participation.

### Inclusion criteria

>18 years old;Resting ankle brachial pressure index (ABPI) <0.9;Able to walk unaided;English speaking and able to follow exercise instructions;Able to provide informed consent.

### Exclusion criteria

Those who have critical limb-threatening ischaemia (rest pain and/or
tissue loss);Those undergoing active cancer treatment;Those presenting with any significant comorbidities or contraindications
to exercise testing or training in accordance with the American College
of Sports Medicine;^
22
^Unstable/uncontrolled coronary heart disease.

### Study procedures

An outline of the participant pathway for the study is presented in Figure 1. Once referred,
patients will be contacted by a member of the research team. Eligible patients
will be offered the opportunity to participate in this study and receive a
participant information sheet. A subsequent phone call (at least 48 h later)
from the research team will confirm those who wish to participate. Informed
consent will be obtained at the baseline assessment visit. Baseline procedures
will include: a clinical examination, a treadmill walking test, anthropometrics,
barriers to physical activity and quality-of-life questionnaires. Patients will
also be asked to wear a physical activity monitor for a duration of 7 days
following the baseline assessment. Eligible participants will subsequently be
randomised to 24 weeks of twice-weekly PF, MOD-P or MAX-P SEP. All measures
completed at baseline will be repeated at 12 and 24 weeks. Semi-structured
interviews will be conducted at 24 weeks to evaluate patient acceptability,
tolerability and enjoyment. Those who decline study participation will still be
offered SEP participation as part of usual care.

**Figure 1. fig1-17539447221108817:**
[figure not shown]
Study flow chart.

### Intervention

The SEP will consist of a circuit^
23
^ (Figure 2)
lasting for 60 min, including a 10-min warm-up and cooldown.^
24
^ Participants will be individually prescribed exercise until they achieve
the desired rating of claudication pain on each station within 3–5 min. They
will start the next exercise once the pain has subsided. The American
Association of Cardiovascular and Pulmonary Rehabilitation (AACVPR) 0–4 scale to
rate claudication pain will be adopted (Figure 3). Participants in the PF group
will cease exercise at the onset of claudication (1 on the rating scale), the
MOD-P group will stop once moderate pain is achieved (2 on the rating scale) and
the MAX-P group will stop once maximal pain is achieved (4 on the rating scale).
Participants who are unable/unwilling to comply with the protocols (achieve
desired rating of claudication pain) will be permitted to cease involvement and
continue with usual-care SEP. To be regarded as having sufficiently adhered to
the treatment protocol, patients must complete a minimum of 80% of sessions over
24 weeks (38 of 48).

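### Participants who do not reach their assigned pain level may cease involvement, and nothing keeps them in the 12- and 24-week assessments that the intention-to-treat analysis needs

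*Protocol article*

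**What the plan says.** In the protocol article, the Intervention section sets a pain target for each arm on the 0–4 scale: 1 for PF, 2 for MOD-P and 4 for MAX-P. Participants who are unable or unwilling to achieve the "desired rating of claudication pain) will be permitted to cease involvement and" "continue with usual-care SEP". Adherence in the same section requires at least 80% of sessions, given as 38 of 48.

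Under Study procedures, all measures "completed at baseline will be repeated at 12 and 24 weeks". Tolerability is covered by interview: "interviews will be conducted at 24 weeks to evaluate patient acceptability". People who decline the study are also offered the SEP as usual care.

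Outcome assessments says that sessions attended and completed are recorded, as is drop-out from the SEP in every group, with reasons where volunteered.

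Under Data analysis, "All analyses will be performed on an" intention-to-treat basis, with baseline MWD as a covariate in the primary ANCOVA.

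The Introduction states: "When exercise is prescribed at higher levels of pain, completion rates are" lower.

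**The concern.** Two events are run together: stopping the allocated exercise, and leaving the trial. These participants go on exercising in usual care, so what ends is most naturally read as their part in the study. No section says that they still attend the 12- and 24-week treadmill tests.

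The trigger is the randomised factor itself. A PF participant has to reach only the onset of pain, whereas a MAX-P participant has to reach the top of the scale. With the Introduction's remark on completion, this makes unequal loss between arms a well-supported risk. The loss may also be related to the primary outcome, because MWD is recorded when claudication pain stops the patient walking.

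If the outcomes of these participants are not collected, an analysis labelled intention-to-treat would rest on those who tolerated or achieved their assigned target. An analysis plan can specify how to handle missing values, but it cannot recover treadmill tests that were never done.

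The interviews have a related, smaller weakness. They are held at 24 weeks, so people who stopped earlier because of pain are likely to be under-represented on tolerability.

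**Working it through.** **1. The plan's own figures.** Inputs from Sample size: difference 143 m, SD 111.3 m, power 90%, significance level 5% (two-sided, from Data analysis).

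- Per arm, normal approximation: 2 × (1.960 + 1.282)² × (111.3/143)² ≈ 12.7, rounded up to 13. Three arms give 39, as stated. The article does not name the test used in G*Power, so this is one route to the figure.
- Drop-out: 39 × 1.3 = 50.7, rounded up to 51, as stated.
- Losses that still leave 39: 51 − 39 = 12, or 12/51 = 23.5%.

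The plan therefore expects some outcomes to be lost. It does not split that loss by arm.

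**2. Completers' bias with no true arm difference.** Assumptions not in the documents: loss of 20% v 40% or 15% v 45% in the low- and high-pain arms, and a correlation r of 0.3 to 0.7 between the tendency to stay and the change in MWD.

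Shift of the completers' mean in an arm = r × SD × φ(z) / (1 − loss), where z is the normal quantile for that loss and φ the normal density.

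- φ(z)/(1 − loss): 20% gives 0.350, 40% gives 0.644, 15% gives 0.274, 45% gives 0.720.
- Difference between arms × 111.3 m: (0.644 − 0.350) × 111.3 ≈ 32.7 m, and (0.720 − 0.274) × 111.3 ≈ 49.6 m. Each is then multiplied by r.

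| r | 20% v 40% | 15% v 45% |
|---|---|---|
| 0.3 | 9.8 m | 14.9 m |
| 0.5 | 16.4 m | 24.8 m |
| 0.7 | 22.9 m | 34.7 m |

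The range of about 10 to 35 m is 7% to 24% of 143 m. With r positive, the high-pain arm looks better than it is. With r negative, the same sizes run against it.

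**3. A second model as a check.** Assume that a fraction q of MAX-P leaves, that leavers' change is D standard deviations worse than stayers', and that exit from PF is unrelated to outcome. Bias = q × D × 111.3 m.

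- q = 0.1, D = 0.5: 5.6 m.
- q = 0.3, D = 0.5 to 1.0: 16.7 to 33.4 m.
- q = 0.5, D = 1.0: 55.7 m.

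In a simulation with 17 per arm and 10% random loss in PF, the type I error of a nominal 5% test rose to between 5.4% and 17% over q = 0.1 to 0.5. At q = 0.3 it was about 6% to 10%.

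**4. Power.** By normal approximation at the unadjusted 5% level, pairwise power for 143 m is about 96% with 17 per arm, 91% with 13 v 13, 90% with 15 v 11 and 86% with 15 v 9. Moderate imbalance costs little power; the main issue is bias.

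**5. Adherence threshold (separate).** 0.80 × 48 = 38.4 sessions, and 38/48 = 79.2%. The printed count falls below the printed minimum percentage.

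**The case against.** **Contradiction with intention-to-treat.** A reader might infer that the exit rule flatly contradicts the analysis principle. The documents do not go that far. The wording is permissive, it stands under Intervention, and no section says that follow-up ends or that these participants are left out of the analysis. Stopping the allocated exercise is compatible with intention-to-treat if patients are still assessed and analysed as randomised. Fuller procedures may stand in documents not shown. What remains is that the one rule stated does not separate the two events, and its natural reading is exit.

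**Certain bias towards MAX-P.** A reader might also infer that the rule will remove more MAX-P patients and favour the arm that the article cautiously expects to do best. No arm-specific rates are given. Those unable to achieve the target may include good walkers who do not reach maximal pain within the 3–5 minutes at a station, and losing them would push the other way. Unequal loss is a risk, and its direction is an assumption.

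**Survivor bias in adherence.** This does not follow. Sessions and drop-out are recorded in all groups, so a leaver counts as a drop-out with few sessions completed.

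**Size.** The 10 to 35 m is below one standard error of a pairwise difference at 13 per arm (111.3 × √(2/13) ≈ 44 m), and the baseline-MWD covariate may absorb some of the selection. Both points are fair, but a systematic shift is not removed by being smaller than the random error. The scenarios average 30% loss, and 30% of 51 is about 15. The room left by the plan's own numbers is 12.

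**Conclusion.** The point holds as a gap in a stated conduct rule. Participants may cease involvement for failing the randomised pain target, and nothing in the article keeps them in the assessments on which the intention-to-treat analysis depends. Loss may then differ by arm and be related to MWD.

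The 10 to 35 m is an illustration. It rests on assumed loss rates and on a correlation between staying and response; only the SD comes from the plan. The second model, with other assumptions, gives about 6 to 56 m. Neither establishes which arm would gain.

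The change is worth making because it is cheap and missed assessments cannot be made good afterwards. The 38-of-48 mismatch is a small, separate slip, and no analysis described in the article depends on it.

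**What to change.** In the Intervention section, replace the exit sentence with wording such as: *Participants who stop the allocated exercise may continue with usual-care SEP and remain in the trial. They will be invited to all 12- and 24-week assessments and analysed in the arm to which they were randomised. Only withdrawal of consent ends follow-up.*

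Under Study procedures, add that participants who stop are invited to the tolerability interview when they stop.

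Separately, reconcile the adherence percentage with the session count.

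The cost is a minor amendment for ethics approval, matching consent wording and a small number of extra assessment visits. Testing takes place at the SEP sites, so the added travel is probably modest, although the article does not say which site's usual-care SEP these participants would attend. No patient's exercise or right to stop changes.
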